1. INVESTIGATIONAL PLAN
   1. Overall Study Design and Plan

This is a multi-centre, controlled study utilising a randomised switching design for cigarette smoking and NGP use. Three separate populations will be recruited:

- Continue-to-smoke/THP population (n = 265)
- Intend-to-quit population (n = 190)
- Never-smoked population (n = 40)

Subjects in the continue-to-smoke/THP population will be randomised to 1 of the following study arms:

- Arm A – continue to smoke commercially manufactured filter cigarettes and/or roll your own cigarettes (n = 65)
- Arm B – switch to THP1.1(RT) THP (n = 200)

The aim is for 65 subjects (Arm A) and 200 subjects (Arm B) to be randomised, with the intention for a minimum of 50 subjects to complete per arm.

Subjects in the intend-to-quit population will be assigned to the assisted smoking cessation arm (Arm D). The aim is to recruit 190 healthy adult male and female regular smokers of 10 to 30 non-mentholated commercially manufactured filter cigarettes and/or roll your own cigarettes per day, and who are intending to cease all non-medicinal nicotine use. This group will be supported with NRT and/or varenicline as appropriate. The intended minimum number to complete is 50 subjects.

Subject in the never-smoked population will be assigned to Arm E. The aim is to recruit 40 subjects who have never smoked (<100 cigarettes in their lifetime and none in the 30 days prior to Screening), with the intention for a minimum of 30 subjects to complete.

A schematic of the study design is presented in Figure 1.

Figure 1: Study Schematic

*Subjects in Arm E will only attend Screening, Visit 1 (Day 1), Visit 4 (Day 90 +/- 3 days), Visit 7 (Day 180 +/- 2 weeks), Visit 13 (Day 360 (+/- 2 weeks), and Follow-up.

- - 1. Duration

This will be an ambulatory study, with subjects in Arms A, B, and D attending clinic visits at Screening, Day 1, Days 30, 60, and 90 (+/-3 days), Days 120, 150, 180, 210, 240, 270, 300, 330, and 360 (+/- 2 weeks), and at Follow-up (within 28 days following last visit). Subjects in Arm E will attend clinic visits at Screening, Day 1, Day 90 (+/-3 days), Days 180 and 360 (+/- 2 weeks), and at Follow-up (within 28 days following last visit).

Subjects will be randomised (Arms A and B) or enrolled (Arms D and E) on Day 1. Subjects will undergo screening within 28 days prior to Day 1, and will return for a Follow‑up Visit within 28 days of Day 360.

- - 1. Study Arms

Subjects will be randomised (Arms A and B) or assigned (Arms D and E) to one of the study arms presented below.

| **Study Arm** | **Recruitment Population** | **Randomised Product Use** |
| --- | --- | --- |
| A | THP/continue-to-smoke population | Continue to smoke subject’s usual brand of commercially manufactured filter cigarettes and/or roll your own cigarettes |
| B |  | THP1 (THP1.1(RT)) |
| D | Intend-to-quit population | None |
| E | Never-smoked population | None |

- - 1. Product Use

In Arms A, B and D, the subject will be asked to continue smoking their usual brand of cigarette until randomisation (Arms A and B) or enrolment (Arm D) on Day 1.

Subjects in Arms A and B will use only their assigned product following randomisation until Check-out from the final non-residential clinic visit on Day 360. Subjects in Arm D will use only specific NRT/smoking cessation aids as described in Section 3.4.2 following enrolment until Check-out from the final non-residential clinic visit on Day 360. Subjects in Arm E will not use any products/NRT/smoke cigarettes during the study.

For Arms A and B, smoking/product use following randomisation will be *ad libitum*, subject to an average product use of up to 200% of their self-reported cigarettes per day at Screening. Subjects will be reminded of the risks associated with smoking prior to enrolment onto the study and that they are free to voluntarily quit smoking and/or withdraw from the study at any time (Section 3.4).

For subjects in Arm B:

- At Visit 1, subjects in Arm B will be provided with no more than 150% of their self‑reported cigarettes per day (CPD), with the provision to obtain the remaining 50% before Visit 2 by visiting the site.
- At Visits 2 to 12, an assessment of product usage should be undertaken, and the allocation of product should be 120% of the product used in the previous period, up to the limit of 200% (self-reported pre-study CPD). At these visits, subjects will return all empty, part-used, and unused packs of THP consumables.
- At Visit 13, subjects will return all empty, part-used, and unused packs of THP consumables, and the study device, chargers and other accessories supplied to them for this study.

Subjects randomised to Arm A will continue to smoke their usual brand of cigarettes at their own expense.

- 1. Justification of Study Design

Subjects in this study will be a minimum of 23 years of age. This is based on:

- The legal age to obtain tobacco products in the United Kingdom is 18 years
- Subjects will be required to have a smoking history of at least 5 years

To investigate the effects of smoking cessation over 12 months in smokers, a population of subjects who are intending to quit smoking will be recruited. It is anticipated that a higher proportion of these subjects will not complete the study, in comparison to recruiting subjects who are not intending to quit. Having an intend-to-quit population will also reassure subjects who do not want to quit smoking (the continue-to-smoke/THP population) that they will not be randomised to the cessation arm, thus aiding recruitment.

The BoE selected as endpoints in this study are based around the initial list of priority toxicants proposed by the WHO Study Group on Tobacco Product Regulation.^18^

The biomarkers of biological effect (BoBE) selected for evaluation are markers for bronchodilation/vascular tone, platelet activation, coagulation, oxidative stress, tissue remodelling, inflammation/chemokine, endothelial dysfunction, metabolic status, and nitrosative stress. Within the categories mentioned above, endpoints have been selected to support various events within the biological pathway of interest that they pertain to (e.g. finger plethysmography, endothelin-1, 3-nitrotyrosine, and NO are all related endpoints to support the mechanisms which control vascular tone and endothelial function).

- 1. Subject Withdrawal Criteria

Subjects may be withdrawn from the study prematurely for the following reasons:

1. If a subject experiences an intolerable AE, premature discontinuation will be at the discretion of either the Investigator or their appropriately qualified designee, or the subject, independent of the relationship of the AE to the study test product. The appropriate AE electronic Case Report Form (eCRF) page must be completed.
2. If a subject develops a non-fulfilment of inclusion/exclusion criteria or concurrent disease, which at the discretion of the Investigator (or their appropriately qualified designee) or the Sponsor, no longer justifies the subject’s participation in this study.
3. If any deviations occur during the conduct of the study. This may include the subject’s erroneous inclusion in the study. Any protocol deviations detected during the study should be corrected when possible and the subject should be allowed to continue. All protocol deviations will be fully documented and considered for their effect on study objectives. Deviations that could lead to subject discontinuation from the study include:

- deviations which could affect subject’s safety (e.g. illness requiring treatment[s]) which in the clinical judgement of the Investigator or their appropriately qualified designee (or after discussion with the Medical Monitor [details provided in Section 8.4]) might invalidate the study by interfering with the allocated test product or the willingness of the subject to comply with the study activities.
- deviations involving the use of any nicotine/tobacco products other than the intended conventional cigarettes or THP by subjects in Arms A and B. The level of non-compliance that results in subject withdrawal from the study will be determined by the Sponsor.
- deviations involving the use of any nicotine/tobacco products by Arm D (the cessation arm) after Visit 1 and before Check-out at Visit 13, excluding specified NRT/smoking cessation aids described in Section 3.4.2. The level of non-compliance that results in subject withdrawal from the study will be determined by the Sponsor.
- deviations involving the use of any nicotine/tobacco products by subjects in Arm E (never-smoked arm).

1. If the subject is uncooperative, including non-attendance. In these cases, efforts should have been made by the Investigator or their appropriately qualified designee to ascertain the reason and to ensure subject’s attendance as soon as possible.
2. Subject’s personal request: the subject could decide, at any moment of the study, to stop his/her participation. The Investigator or their appropriately qualified designee should ensure this is not due to AEs, in which case, this reason should be selected. Subjects do not have to provide a reason for withdrawing from the study if they do not wish to do so (reason for withdrawal should be recorded as ‘not given’).
3. Pregnancy.
4. Premature cancellation of the study.
5. If a subject in a smoking/THP arm (Arms A and B) decides to quit smoking following Screening until Check-out at Visit 13.
   1. Smoking Advice and Support
      1. All Subjects

Information will be provided for all subjects regarding the health risks associated with smoking. Advice on smoking cessation will be freely available to all subjects at Screening and during all clinic visits. The advice will be based on the recommendations of the WHO “Evidence based Recommendations on the Treatment of Tobacco Dependence”. Subjects who decide to quit smoking during the study period will be referred to the appropriate stop smoking services to support their cessation attempt.

- - 1. Smoking Cessation Arm (Arm D)

Subjects in Arm D will determine their smoking cessation strategy with the Investigator or their appropriately trained designee at Visit 1. If necessary, subjects will be provided with NRT and/or varenicline (Champix; 1 × 12 week course) or given a prescription for these products. Subjects will also be provided smoking cessation counselling at the site. For additional support, subjects will be referred to the following services based on where they live:

Subjects in England - National Health Service (NHS) quitting support website (https://www.nhs.uk/live-well/quit-smoking/nhs-stop-smoking-services-help-you-quit), the Smokefree helpline ([contact]), online advisor support, local stop smoking service, and Smokefree app.

- Subjects in Northern Ireland – Want2Stop quitting support website (www.want2stop.info)
- Subjects in Wales – NHS Wales quitting support website (www.helpmequit.wales) and telephone helpline ([name])

Subjects will also be provided with a 24-hour site number that they contact for cessation support if required. The Investigator or their appropriately qualified designee will review subject’s progress and strategy at each clinic visit.

- 1. Management of Subject Safety

Before leaving the clinical site, each subject will be given a card to carry at all times in case of an emergency or should they otherwise require assistance outside the clinical site. The card gives details of the study number, start and end date of the subject’s involvement in the study, subject details, name of the relevant study physician and the address and telephone number of the clinical site. Subjects may destroy this card 4 weeks after Visit 13.

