| Study Design: | This is a multi-centre, controlled study utilising a randomised switching design for cigarette smoking and THP use. Three separate populations of subjects will be recruited and randomised/enrolled as follows:   \| **Population** \| **Study arm and randomised product** \| \| --- \| --- \| \| Continue-to-smoke/THP population \| Arm A – conventional cigarettes  Arm B – THP1.1(RT) \| \| Intend-to-quit population \| Arm D – assisted smoking cessation \| \| Never-smoked population \| Arm E – never-smoked \|   This study will be ambulatory, with subjects in Arms A, B, and D attending a total of 13 non-residential clinic visits (approximately 1 every 30 days) plus a Screening Visit and a Follow-up Visit over a period of 12 months. Subjects in Arm E will attend a total of 4 non‑residential clinic visits (Day 1 and approximately 3, 6 and 12 months post-enrolment) plus a Screening Visit and a Follow-up Visit. |
| Number of Subjects: | It is planned for 495 subjects to be enrolled into Arms A, B, D, and E, with the aim of 180 subjects completing the study. It should be noted that 34 subjects had been randomized into Arm C prior to issue of Amendment 7. |

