1. OBJECTIVES AND ENDPOINTS
   1. Primary Objective

- To quantitatively assess differences in primary study endpoints at 90, 180, and 360 days between subjects who continue to smoke conventional cigarettes and subjects who switch to a THP.
  1. Secondary Objectives
- To quantitatively assess differences in secondary study endpoints between subjects who continue to smoke conventional cigarettes and subjects who switch to a THP.
- To assess differences in all study endpoints between subjects who switch to a THP and subjects in the assisted smoking cessation arm.
- To assess the differences in all study endpoints between subjects who switch to a THP or undertake assisted smoking cessation, and subjects who have never smoked.
- To monitor the safety profile of subjects using THPs and combustible cigarettes, and subjects in the smoking cessation and never-smoked arms.
  1. Exploratory Objectives
- To quantitatively assess the time required to observe changes in selected primary and secondary endpoints following a switch from conventional cigarettes to a THP or assisted cessation.
- To quantitatively assess differences in the exploratory endpoints between subjects who continue to smoke conventional cigarettes, subjects who switch to a THP, subjects in the cessation arm, and subjects who have never smoked (to be reported separately).
- To investigate the profile of selected primary and secondary endpoints over the course of the study for each study arm.
  1. Endpoints
     1. Primary Endpoints

Primary endpoint biomarkers to be assessed are presented in the following table:

| **Biomarker** | **Abbreviation** | **Matrix** | **Indication** |
| --- | --- | --- | --- |
| Total 4-(methylnitrosamino)-1-(3-pyridyl)-1-butanol | Total NNAL | Urine  (24-hour) * | Metabolite of the smoke toxicant 4-(methylnitrosamino)-1-(3-pyridyl)-1-butanone (NNK) |
| 8-epi-prostaglandin F_2α_ Type III | 8-Epi-PGF_2α_ Type III | Urine  (24-hour) * | Marker of oxidative stress |
| Augmentation Index | AIx | Physiological measure | Marker of arterial stiffness and hence an indicator for cardiovascular risk |

* ambulatory collection.

- - 1. Secondary Endpoints

Secondary endpoint biomarkers to be assessed are presented in the following table:

| **Biomarker of Exposure** | **Abbreviation** | **Associated Toxicant** | **Matrix** |
| --- | --- | --- | --- |
| Carbon monoxide†† | CO | Carbon monoxide | Exhaled breath |

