For subjects in Arm B, an assessment of product usage should be undertaken, and the allocation of product should be 120% of the product used in the previous period, up to a limit of 200%. At these visits, subjects will return all empty, part-used, and unused packs of THP consumables. At Visit 13, subjects will return all empty, part-used, and unused packs of THP consumables, and the study devices, charger, and other accessories supplied to them for this study.

- 1. Follow-up Contact
     1. Visits 1 to 12

All subjects in Arms B and D will be contacted by telephone 7 to 14 days after Visit 1 to aid randomised product (Arm B) or smoking cessation (Arm D) compliance. Subjects will be reminded of the support available (see Section 3.4), and will be able to speak to an appropriately trained member of staff to help to prevent combustible cigarette use.

At the discretion of the Investigator or their appropriately trained designee, additional telephone calls or clinical site visits may be scheduled for subjects in Arm D to monitor or update their smoking cessation strategy or prescriptions.

- - 1. Visit 13

All subjects will return to the site for a Follow-up assessment within 28 days after Check-out at Visit 13. The Investigator or their appropriately qualified designee will complete the following safety assessments:

- Physical examination (symptom driven)
- Vital signs
- 12-lead ECG
- Review of AEs/SAEs
- Clinical laboratory evaluations
- Review of concomitant medication.

For female subjects:

- Urine pregnancy test.

Provided there are no AEs which require further attention, the subject’s participation in the study will be complete. A further visit may be scheduled if deemed necessary by the Investigator or their appropriately qualified designee.

Subjects who, after enrolment, discontinue the trial prematurely should be encouraged to participate in this follow-up procedure. If their withdrawal is due to safety evaluations then the subjects should be followed until these return to baseline levels or until the Investigator or their appropriately qualified designee has determined that these events are no longer clinically significant.

Subjects who develop an AE at any time during the study will be followed until any required evaluations have returned to baseline or until the Investigator or their appropriately qualified designee has determined that these events are no longer clinically significant.

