Adverse events requiring hospitalisation should be considered serious. In general, hospitalisation signifies that the subject has been detained (usually involving an overnight stay) at the hospital or emergency ward for observation and/or treatment that would not have been appropriate at the clinical site. When in doubt as to whether hospitalisation occurred or was necessary, the AE should be considered serious.

Hospitalisation for elective surgery or routine clinical procedures, which are not the result of an AE, need not be considered AEs and should be recorded on a clinical assessment form and added to the eCRF. If anything untoward is reported during the procedure, this must be reported as an AE and either ‘serious’ or ‘non-serious’ attributed according to the usual criteria.

- 1. Assessment of Adverse Events

The condition of each subject will be monitored from the time of signing the ICF, to Check‑out at the Follow-up Visit. In addition, any signs or symptoms will be observed and elicited at each visit by open questioning, such as “How have you been feeling since your last visit ?”

Subjects will also be encouraged to spontaneously report AEs occurring at any other time during the study.

Any AEs and remedial action required will be recorded in the subject's source data. The nature, time of onset, duration and severity will be documented, together with the Investigator’s opinion of the relationship to product use.

Any clinically significant abnormalities identified during the course of the study will be followed-up until they return to normal or can be clinically explained.

- 1. Intensity of Adverse Events

The causal relationship between an AE and the study product is defined as follows:

**Not Related** The AE is definitely caused by the subject's clinical state or the study procedures/conditions.

**Unlikely Related** The temporal association between the AE and the product is such that the product is not likely to have any reasonable association with the AE.

**Possibly Related** The AE follows a reasonable temporal sequence from the time of product use but could have been produced by the subject's clinical state or the study procedures/conditions.

**Related** The AE follows a reasonable temporal sequence from the time of product use, abates upon discontinuation of the product and reappears when the product is reintroduced.

The severity of an AE will be recorded as one of the following:

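### AEs are asked about at 12 post-baseline visits in Arms A, B and D but at 3 in Arm E, so descriptive AE comparisons with never-smokers probably under-count mild, short-lived events in Arm E

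*Protocol*

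**What the plan says.** **Visits.** The Synopsis has Arms A, B and D "attending a total of 13" non-residential visits. For Arm E it gives four "clinic visits (Day 1 and approximately 3, 6 and 12 months post-enrolment". Section 3.1.1 lists the days. After Days 30, 60 and 90, Arms A, B and D come on "Days 120, 150, 180, 210, 240, 270, 300, 330, and 360 (+/- 2 weeks), and at Follow-up (within 28 days following last visit". For the never-smokers: "Subjects in Arm E will attend clinic visits at Screening, Day 1, Day 90 (+/-3 days), Days 180 and 360 (+/- 2 weeks". All arms also have a Follow-up visit with an AE review (Section 6.4.2).

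**AE enquiry.** Under Section 8.2, "any signs or symptoms will be observed and elicited at each visit by open questioning", and the example question is "How have you been feeling since your last visit". The same section encourages unprompted reports between visits in every arm.

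**Examinations.** Appendix 15.1, footnote j, limits Visits 2, 3 and 10 to Arms A, B and D. All three include a symptom-driven physical examination and lung function tests. Visit 10 also has vital signs, ECG and laboratory tests.

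**Use of the data.** A secondary objective (Section 2.2) is to compare, on every endpoint, "subjects who switch to a THP or undertake assisted smoking cessation, and subjects who have never smoked". AE/SAE recording is in the secondary endpoint table (Section 2.4.2), with a dagger that leaves any statistical method to the SAP. Section 9.4 summarises all safety data by arm in the safety population and does not limit this to visits that the arms share.

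**The concern.** When enquiry is tied to attendance, the visit schedule determines how often a subject is asked and how far back the subject must remember. Arms A, B and D are asked after about 30 days; Arm E is asked after about 90, 90 and 180 days. A cold, headache or short bout of cough is more easily forgotten over the longer period. Extra scheduled examinations also give Arms A, B and D more occasions for a clinically relevant finding to be recorded as an AE (Sections 8.4.1 and 8.4.2).

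Arm E is the study's only never-smoked reference. If its counts are low partly because its subjects were asked less often, the background AE rate looks too low. The gap between THP use or cessation and never smoking then looks too wide. Unequal questioning would be read as a difference in harm.

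**Working it through.** **1. Visit counts.** From the days in Section 3.1.1:

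- Arms A, B, D: Day 1 plus Days 30, 60, …, 360 gives 1 + 12 = 13.
- Arm E: Day 1 plus Days 90, 180, 360 gives 1 + 3 = 4.

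Both reproduce the Synopsis totals.

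**2. What the schedule gives each arm after Day 1**

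| | Arms A, B, D | Arm E |
|---|---|---|
| AE enquiries through Day 360 | 12 | 3 |
| … with Follow-up | 13 | 4 |
| First scheduled enquiry | Day 30 | Day 90 |
| Time since last visit (days) | 29, then 30 | 89, 90, 180 |
| Vital sign/ECG/laboratory sets through Day 360 | 4 (Visits 4, 7, 10, 13) | 3 (Visits 4, 7, 13) |
| … with Follow-up | 5 | 4 |
| Physical examination and spirometry sets through Day 360 | 6 (Visits 2, 3, 4, 7, 10, 13) | 3 (Visits 4, 7, 13) |

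The enquiry ratio is 12/3 = 4, or 13/4 = 3.25 with Follow-up. In Arm E, 3 × 30 = 90 of 360 days (25%) fall within the 30 days before an enquiry. In Arms A, B and D all 360 do.

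**3. Possible size (assumed model).** The protocol gives no recall or AE-rate figures. Assume the same true rate in all arms, onsets spread evenly over 360 days, no spontaneous reporting, and a chance of recall that halves every h days. With τ = h/ln 2, the captured share is

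c = Σ τ(1 − e^(−L/τ)) / 360,

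summed over visit intervals L: twelve of 30 days, or 90, 90 and 180 days. For h = 30, τ = 43.28:

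- Arms A, B, D: 43.28 × (1 − 0.5)/30 = 0.721
- Arm E: 43.28 × (0.875 + 0.875 + 0.984)/360 = 0.329
- Shortfall: 1 − 0.329/0.721 = 54%

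| Half-life h (days) | c, Arms A, B, D | c, Arm E | Fewer in Arm E |
|---|---|---|---|
| 30 | 0.721 | 0.329 | 54% |
| 60 | 0.845 | 0.521 | 38% |
| 90 | 0.893 | 0.631 | 29% |
| 180 | 0.944 | 0.783 | 17% |

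**4. Effect of spontaneous reporting.** If a share s of events is reported unprompted in every arm, the captured share becomes s + (1 − s)c. The shortfall is then (1 − s)(c_ABD − c_E) / [s + (1 − s)c_ABD]. It falls steadily as s rises and is zero at s = 1. The table is therefore an upper limit for each half-life.

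**5. Common windows.** If only onsets in the 30 days before a shared visit count, every arm captures τ(1 − e^(−30/τ))/30. The ratio is then 1.00 for any half-life.

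**The case against.** The strongest reply is that no formal AE comparison with Arm E is planned. Safety has its own objective, which is only to monitor. Section 9.3 specifies only THP versus Arm A contrasts, and Section 9.4 is descriptive. Arm E is non-randomised, with 40 subjects and a size set empirically, so an AE difference from it would not be a causal estimate even with identical visits. The dagger leaves AE methods to a SAP not shown here. Fewer visits for an unexposed reference group is a reasonable saving of burden.

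Much of this stands. It limits the weight of the point and means that the absence of an analysis rule in the protocol is not itself a fault. It does not remove the point. The schedule is fixed in the protocol, the Section 2.2 objective covers AEs as written, and a SAP can restrict a comparison but cannot recover events that were never elicited.

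Mitigation also counts. Spontaneous reporting is encouraged, subjects must consult the investigator before taking any medicine (Section 7.1.1), and all carry a card with the site's telephone number (Section 3.5). These apply equally in every arm. They reduce the gap but do not equalise prompted enquiry.

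A reader might infer more than the documents support:

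- **That Arm E will lose 17% to 54% of its AEs.** Those figures rest on assumed half-lives and no spontaneous reporting.
- **That every abnormal laboratory value is an AE.** Section 8.4.1 requires a judgement of clinical significance.
- **That the early telephone call is a further AE enquiry.** "All subjects in Arms B and D will be contacted by telephone 7 to 14 days after Visit 1", but its stated purpose is compliance and no AE question is specified. It is only an extra chance to report.
- **That the randomised comparison is biased.** Arms A and B share one clinic schedule.
- **That the imbalance could make the THP look falsely safe against never-smokers.** The likely direction is the opposite.

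**Conclusion.** The point holds for descriptive AE comparisons of Arms B or D with Arm E. The unequal schedule is certain: 12 against 3 prompted enquiries (13 against 4 with Follow-up), 4 against 3 vital sign/ECG/laboratory sets (5 against 4 with Follow-up) and 6 against 3 physical examination and spirometry sets through Day 360. The consequence is likely but not measured: mild, short-lived events are probably under-counted in Arm E.

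The size cannot be taken from the documents. It depends on how quickly subjects forget and how much they report unprompted. SAEs and long-lasting conditions should be less affected. The primary objective is untouched. This is a matter of how the Arm E safety data are presented and read, and it deserves correction because the correction is cheap.

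**What to change.** 1. Keep the full-period by-arm AE summaries for all arms. Add a footnote that non-serious AE counts in Arm E are not comparable with the other arms because its subjects were asked less often.
2. Add one supplementary table for comparisons with Arm E. In every arm, limit it to AEs with onset in the 30 days before Visits 4, 7 and 13 (actual visit dates) plus the Follow-up period, and to examination, laboratory, ECG and spirometry findings at those common visits.
3. Report SAEs over the whole study in all arms.

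This needs SAP wording and one extra table set, built from onset dates that Section 8.4 already records. It needs no change to the visit schedule.

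The costs are real. The windows before the three visits cover 90 of 360 days, so there are fewer events and less precision. They omit roughly Days 1 to 60, just after switching or quitting, which includes most of the 12-week varenicline course mentioned in Section 3.4.2 for Arm D. Onset dates in Arm E still come from a question spanning 90 to 180 days, so they may be less exact. The table must therefore supplement the full summary and not replace it.
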